#### Skeletal muscle torque and fatigue

Skeletal muscle torque and fatigue of the knee extensor muscle groups (left and right) will be evaluated at baseline, after 12 weeks at P1 and then 12 weeks after FES-LEC for both groups at P2 using a Biodex isokinetic dynamometer (Biodex Medical Systems, Shirley, NY, USA). Participants will be in a seated posture with the trunk-thigh angle and the knee flexed at 90° (where 0 corresponds to full knee extension). Isometric torque will be measured after adjusting the amplitude of the current to 50 and 100 mA (frequency 30 Hz and pulse duration 450 μs). Fatigue will be assessed by measuring the torque elicited at 10, 20, 30, 40, 50 60, 80, and 100 Hz before and immediately after intervention. Isokinetic torque will be measured at 60, 90, and 180 degrees/s using the same electrical stimulation protocol [19].

#### Skeletal muscle biopsy

Three biopsy samples of the vastus lateralis muscle (100 mg wet wt.) will be obtained by a 14-gauge Tru-Cut needle to compare the effects of evoked NMES + FES versus control on protein levels of IRS-1, GLUT-4, IGF-1 and PGC-1 α, AMPK, Akt and mTOR as well as the phosphorylation forms of AMPK, AKT, and mTOR. We will also test whether NMES + FES enhanced mitochondrial enzymatic activities and ETC compared to control. Skeletal muscle biopsies of the right vastus lateralis muscle will be obtained before training and after 12 and 24 weeks of interventions [48, 49].

Western blot analysis will be performed to determine the protein concentrations as previously described [50]. Briefly, proteins will be resolved by SDS-PAGE then transferred to two supported nitrocellulose membranes by wet electromembrane transfer at 110 V for 2 h and then blocked in 6% bovine serum albumin (BSA)/Tween-Tris-buffered saline (TTBS) for 1 h. Membranes will be incubated separately with the appropriate primary antibody overnight. The membranes will be washed separately (three times for 20 min) in 6% BSA/TTBS and incubated with appropriate secondary antibody in 4 mL 3% BSA/TTBS at 4 °C for 1 h. The membranes will be washed (four times for 45 min) in 6% BSA/TTBS. Proteins will be visualized using an enhanced chemiluminescence detection system (GE Lifesciences) according to the manufacturer’s instructions. Western blots will be quantified by scanning with A GS800 densitometer. Optical densities of the Western blots will be measured using image-analysis software (Molecular Analyst; Bio-Rad).

#### Mitochondrial electron transport chain activities

Samples of skeletal muscle are studied for assessment of ETC activity. Measurement of maximal enzyme activity is performed in freshly isolated detergent solubilized mitochondria using cholate as detergent. Analysis of freshly isolated samples are initially performed to assure that maximal activity of electron transport complex I is obtained. Skeletal muscle is isolated, homogenized, and a potion subjected to detergent solubilization in cholate. The enzyme activity of ETC complexes is obtained by using specific substrates and inhibitors to isolate segments of the ETC. Assays are performed in 0.1 M phosphate buffer using spectrophotometric endpoints. Complex I activity (NADH coenzyme Q reductase) is measured following the oxidation of substrate NADH to decylubiquinol, a synthetic coenzyme Q, as electron acceptor. Activity is measured in the presence and absence of the specific complex I inhibitor rotenone. In a similar manner, the activity of other complexes is measured using specific substrates, acceptors, and inhibitors. Complex II is measured using succinate as substrate and the reduction of 2,6 dichlorophenolindophenol as the electron acceptor followed as spectrophotometric indicator, with and without thenoyltrifluoroacetone as the inhibitor of complex II. Complex III activity is measured using the reduced synthetic coenzyme Q molecule decylubiquinol as substrate, oxidized cytochrome c as acceptor, and antimycin-A as the complex III specific inhibitor. The reduction of cytochrome c as acceptor is followed as the spectrophotometric endpoint. Complex IV is measured by following the first-order oxidation of added exogenous reduced cytochrome c using azide as the specific inhibitor [51]. Citrate synthase, a tricarboxylic acid cycle component enzyme, is measured as an indicator of mitochondrial mass [51–55].

### Statistical analyses

T-tests and Pearson chi-square tests will be used to compare characteristics that may act as confounding variables, including age, level of injury, time since injury, %FM, as well as the three outcome variables (Si, Sg, VO_2_) to ensure that each group is not different with respect to each variable at baseline. A repeated-measures ANOVA will be performed with glucose effectiveness as the primary study outcome and effects for treatment group (NMES + FES versus control), time (baseline and post-interventions 1 and 2), and the interaction between the two factors included in the model. Similar repeated measured ANOVA models will be fit with each of the body composition, metabolic profile, protein expression, and ETC measures (Aim 3). All statistical analysis will be performed at the 0.05 level with SAS V9.4 (Cary, NC, USA).

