### Recruitment strategy

The recruitment process started in October 2015 and will end in September 2020. Forty-eight participants will be randomly assigned into either NMES + FES or Control + FES groups for 24 weeks. The participants will be matched based on level of injury (tetraplegia versus paraplegia) and time since injury (less than versus more than 10 years) using block randomization using a 2 × 2 design developed by the study statistician. Randomization was conducted using n-query computer program at the baseline before enrollment in the trial (Table 1). Current recruitment status is outlined in Table 2.

**Table 2 Tab2:** The breakdown of the number of persons who have been contacted for the study, who have completed the study, or are currently actively participating in the study. All others have either failed screening or withdrawn from the study

	Study period					
	Pre-Enrolment		Enrolment	Baseline	Post-intervention	
Timepoint**	1	2			1	2
Pre-enrolment:	**536**					
Not-interested	**354**					
Expressed interest	**182**					
Phone screen Failure		**68**				
Physical screen failure		**50**				
Qualified and Enrolled		**64**				
Enrolment [1 = a +b]			**64**			
No Show ^(a)^			29			
Consented ^(b)^ [2=c +d + e + F]			**35**			
Screen Failure ^(c)^			5			
Withdrawn ^(d)^			6	3	1	2
*Completed* ^*(e)*^			21			
*Currently Active* ^*(f)*^			3			
Pending future enrollment ^(g)^			13			
Total sample size [3=b +g]			**48**			
Interventions:						
[NMES+FES]			15	14	13	12
[Control + FES]			15	13	13	12
Assessments:						
[Body Composition Variables]				X	X	X
[Metabolic variables]				X	X	X
[Muscle Biopsy variables]				X	X	X
[Torque and fatigue variables]				X	X	X

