### Sample size

We have acquired pilot data for all outcomes of this project. Glucose effectiveness possesses the smallest effect size from baseline to follow-up with NMES-RT showing a mean baseline effectiveness of 0.01716 and post-treatment mean of 0.02258. Cohen’s *f* was found to be 0.271 using a sample variance of 0.0001 [25]. Assuming the correlation between the pre- and post-treatment measurements is 0.3735 and three total measurements are acquired, 38 individuals will need to complete the study at 90% power using a Type-1 error rate of 0.05. At least 48 participants will need to be recruited, adjusting for a 20% dropout rate. All sample sizes were calculated using the software G*Power (V3.1.9.2). A sample size of 24 was calculated using insulin sensitivity data without regard to dropout rate.

Other factors, such as insulin sensitivity and VO_2_, are considered; each representing larger effect sizes than glucose effectiveness (*f* = 0.313 and *f* = 0.432, respectively). Our study would result in a power of 97.51% and 99.82% for observing the baseline to follow-up difference between the NMES + FES and Control + FES groups, provided the correlation between baseline and follow-up measurements are 0.4 for the outcomes.

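### Entering baseline as an outcome level rather than as a covariate gives away precision in the primary arm comparison; the blocking factors are unmodelled, and baseline tests are asked to guarantee balance

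*Protocol article*

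**What the plan says.** Protocol article, Statistical analyses, names the primary model: "A repeated-measures ANOVA will be performed with glucose effectiveness as the primary study outcome and effects for treatment group", together with "time (baseline and post-interventions 1 and 2), and the interaction between the two factors included in the model". No baseline covariate and no other term is listed.

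The same section plans t-tests and chi-square tests on seven variables (age, level of injury, time since injury, percentage fat mass, insulin sensitivity, glucose effectiveness, VO2), with the aim "to ensure that each group is not different with respect to each variable at baseline". It states no consequence if a test is significant.

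Protocol article, Recruitment strategy, describes the allocation as "matched based on level of injury (tetraplegia versus paraplegia) and time since injury (less than versus more than 10 years) using block randomization", in a 2 × 2 layout. Neither factor reappears as a model term.

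Protocol article, Sample size, assumes that "the correlation between the pre- and post-treatment measurements is 0.3735" and arrives at 38 completers, or 48 recruited.

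**The concern.** Three separate matters meet in one paragraph of the plan.

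- **Baseline handling.** With baseline as a level of time, the arm effect is read from the group-by-time interaction, which compares changes from baseline. Subtracting the whole baseline value is close to optimal only when the correlation is near 1. At 0.3735 it adds more noise than it removes.
- **Blocking factors.** The plan thought level of injury and time since injury important enough to restrict randomisation on them. The Discussion also gives a metabolic reason for level of injury (hepatic glucose production in high lesions). The analysis does not reflect the allocation.
- **Baseline tests.** Under correct randomisation a significant baseline difference is chance, and a non-significant one in a trial of this size does not show balance.

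At stake is mainly precision. Table 2 shows 536 people contacted and 35 consented, so patients are costly here, while the baseline values are collected anyway.

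**Working it through.** **Inputs.** From Sample size: ρ = 0.3735, three measurements, means 0.01716 and 0.02258, variance 0.0001, f = 0.271, 38 completers, 20% dropout; ρ = 0.4 for the other outcomes. Assumptions: equal variance σ² at all visits and the same ρ between every pair of visits. The article gives only one correlation per outcome.

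**1. The plan's own figure.** (0.02258 − 0.01716)/0.01 = 0.542, and f = 0.542/2 = 0.271. For the within-between interaction, λ = f²·N·m/(1 − ρ) = 0.073441 × 38 × 3/0.6265 = 13.36, with 2 and 72 degrees of freedom. Power is 90.4% at N = 38, and 38 is the smallest N reaching 90%. Then 38/0.8 = 47.5, so 48. The stated size reproduces for the model as planned.

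**2. One post-baseline visit against baseline.**

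- Change contrast: 2(1 − ρ)σ² = 1.253σ².
- Baseline as covariate: (1 − ρ²)σ² = 0.860σ².
- Ratio: 2/(1 + ρ) = 2/1.3735 = 1.456, or about 46% more patients for the same precision.
- At ρ = 0.4: 2/1.4 = 1.429, or 43%.

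Cost of estimating p covariates at N = 38: multiply the ratio by (35 − p)/35.

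- Baseline only (p = 1): 1.456 × 34/35 = 1.415 (41.5%).
- Baseline plus two blocking factors (p = 3): 1.456 × 32/35 = 1.331 (33%), if those factors explain nothing.
- Baseline plus the full 2 × 2 strata (p = 4): 1.456 × 31/35 = 1.290 (29%), if the strata explain nothing.

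**3. The planned 2-df test.** Let δ₁ and δ₂ be the arm effects at P1 and P2, Q = δ₁² + δ₂² and S = δ₁ + δ₂. The noncentrality per patient is proportional to:

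- as planned: (Q − S²/3)/(1 − ρ);
- baseline-adjusted: (Q − S²·ρ/(1 + 2ρ))/(1 − ρ), where ρ/(1 + 2ρ) = 0.3735/1.747 = 0.2138.

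| Effect pattern (δ₁, δ₂) | Planned: Q − S²/3 | Adjusted: Q − 0.2138·S² | Ratio |
|---|---|---|---|
| one visit only (0, 1) | 0.667 | 0.786 | 1.18 |
| half at one visit (0.5, 1) | 0.500 | 0.769 | 1.54 |
| equal (1, 1) | 0.667 | 1.145 | 1.72 |

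For same-direction effects S²/Q lies between 1 and 2, so 18% and 72% are the limits. They are before degrees of freedom.

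**4. Blocking factors.** Suppose stratum s adds a constant b to every visit. The planned interaction uses within-person differences, where b − b = 0. With complete data, adding the stratum terms leaves that standard error unchanged. After adjustment for baseline with slope β, the remainder (1 − β)b no longer cancels, so the stratum terms can then help. The article gives no figure for how much. Purely as an assumption, if strata explained 5%, 10% or 20% of the remaining variance, the factor 1/(1 − R²) would be 1.05, 1.11 or 1.25.

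**5. Baseline tests.** Of the seven tested variables, level of injury and time since injury are the two blocking factors and are balanced by the allocation itself. The tests do not affect the precision of the primary analysis; the fault is one of logic.

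**The case against.** The strongest reply is that the planned analysis is sound: randomisation makes a change-type contrast unbiased, and the sample size reproduces for exactly that model. Both points stand. It may also be said that an article condenses a fuller plan. That would excuse missing detail, but here the model terms are listed and baseline is expressly placed among the outcome times. Nor is a repeated-measures layout with baseline in it a defect in itself: constraining the arms to equal baseline means recovers essentially the same efficiency as covariate adjustment. The article states no such constraint.

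Several stronger readings are tempting and do not hold.

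- A reader might take 46% as the loss of the whole plan. It comes only from baseline handling at one post-baseline visit; neither the blocking factors nor the baseline tests contribute to it.
- A reader might infer that omitting the blocking factors inflates the standard error of the planned interaction. Effects constant over time cancel there, and the article does not say that the strata predict change.
- A reader might compute a low power from a single-visit two-arm comparison using the pilot difference. That is not the plan's test, and the pilot difference is a before-after one under NMES-RT, not a difference between arms.
- A reader might infer that participants missing P1 or P2 are discarded. The article names no fitting method or analysis set, and sizing on completers does not define one. This is ordinarily left to the SAP.
- A reader might turn seven baseline tests into a joint false-alarm rate. Counting all seven as independent ignores that two are balanced by design.

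**Conclusion.** The point holds as one of efficiency and specification, not as an error of validity or sample size. At the plan's own correlation, the baseline-to-P2 comparison is as imprecise as if about 46% more patients were needed than with baseline adjustment (41.5% after one degree of freedom). The corresponding figure for the planned 2-df test is about 18% to 72% for same-direction effects. These figures rest on equal variances and, for the 2-df test, on one common correlation across the three visits.

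The blocking factors belong in the model once it is baseline-adjusted, with a gain that the article does not allow one to compute. Using significance tests to secure baseline balance is poor logic and should go. The change is worth making because it uses data already collected.

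**What to change.** Replace the primary model by a repeated-measures model for the P1 and P2 values with arm, visit, arm-by-visit, the baseline value of the outcome and its interaction with visit, level of injury and time-since-injury stratum. An equivalent choice is a model for all three visits with baseline means constrained equal between arms, plus the blocking factors. State that the counterpart of the planned interaction is the joint arm difference at P1 and P2; in the two-visit model the arm-by-visit term alone would test something else. Apply the same form to the other outcomes.

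Delete the baseline t-tests and chi-square tests and give a descriptive baseline table by arm.

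Cost: a few degrees of freedom and revised wording, with no new data, visits or patients. The sample size need not change on this account. The wording should be fixed before outcomes are analysed by arm.

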### Sample size

We have acquired pilot data for all outcomes of this project. Glucose effectiveness possesses the smallest effect size from baseline to follow-up with NMES-RT showing a mean baseline effectiveness of 0.01716 and post-treatment mean of 0.02258. Cohen’s *f* was found to be 0.271 using a sample variance of 0.0001 [25]. Assuming the correlation between the pre- and post-treatment measurements is 0.3735 and three total measurements are acquired, 38 individuals will need to complete the study at 90% power using a Type-1 error rate of 0.05. At least 48 participants will need to be recruited, adjusting for a 20% dropout rate. All sample sizes were calculated using the software G*Power (V3.1.9.2). A sample size of 24 was calculated using insulin sensitivity data without regard to dropout rate.

Other factors, such as insulin sensitivity and VO_2_, are considered; each representing larger effect sizes than glucose effectiveness (*f* = 0.313 and *f* = 0.432, respectively). Our study would result in a power of 97.51% and 99.82% for observing the baseline to follow-up difference between the NMES + FES and Control + FES groups, provided the correlation between baseline and follow-up measurements are 0.4 for the outcomes.

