Functional electrical stimulation (FES) is a form of neuromuscular electrical stimulation (NMES) which provides stimulation of selected muscles in a coordinated manner resulting in a functional pattern such as walking, cycling, or rowing. This is contrary to surface NMES which is used for a single or multiple muscle groups to exercise or to move specific joint, but without the intention of producing a functional or coordinated movement [17]. FES-lower extremity cycling (LEC) is limited by the low exercise intensity, low peak oxygen uptake (0.4 L/min), and rapid muscle fatigue, which renders FES-LEC training a suboptimal modality to increase gain in lean mass and improve metabolic health after SCI [18, 19]. This may result from a mismatch when converting metabolic energy into mechanical energy.

Neuromuscular electrical stimulation (NMES) has been used to evoke exercise-induced resistance training (RT) using regular ankle weights in individuals with chronic SCI [20–24]. Several research groups demonstrated the efficacy of this approach in evoking robust muscle hypertrophy [21, 24, 25]. Dudley et al. showed that eight weeks of twice-weekly NMES RT reverted knee extensor muscle size to 75% of original size at six weeks after SCI [21]. Follow-up studies reported a 35–39% increase in muscle hypertrophy and 33% fatigue resistance of the trained knee extensors [22, 23]. Gorgey et al. noted that 12 weeks of twice-weekly NMES RT elicited an increase in skeletal muscle size of > 35%, decreased IMF and VAT by 25%, and increased insulin sensitivity and insulin growth factor-1 (IGF-1) by 25% [23]. Finally, Ryan et al. noted improvement in mitochondrial capacity by 25% following 16 weeks of twice-weekly evoked NMES RT in persons with chronic complete SCI [24]. A recent study demonstrated that 16 weeks of NMES-RT combined with testosterone replacement therapy (TRT) resulted in a 43% muscle hypertrophy of the knee extensor and 21% increase in thigh muscle cross-sectional area (CSA) accompanied with 14–17% increase in daily basal metabolic rate (BMR) compared to TRT only. [25]

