Today, exercise is still considered a feasible, accessible, and non-pharmacological approach that can overcome several of the cardio-metabolic risk factors after SCI. Upper extremity cycling exercise and/or circuit resistance training are limited to small muscle mass above the level of lesion and do not exercise large muscle groups in the lower extremities. Moreover, persons with tetraplegia (≥ C6 SCI) are less likely to benefit from upper extremity training at intensities that can improve cardio-metabolic risk parameters [63]. This renders exercise limited to use of the upper extremities as an ineffective method to attenuate the deterioration in metabolic profile and body composition after SCI. Another form of exercise is FES-LEC, which effectively restores muscle size and improve of cardio-metabolic risk factors after SCI [64, 65]. However, FES-LES is limited by low exercise intensity, oxygen uptake, and rapid muscle fatigue. To offset for these limitations, the use of hybrid exercise by combining both upper extremities and FES cycling has been shown to improve cardiovascular outcomes more than FES-LEC [66]. Arm cranking exercise (ACE) in combination with FES-LEC displayed increasing muscle oxygenation (StO_2_) at 40%, 60%, and 80% of individuals’ peak VO_2_ compared to ACE only that showed decreases in StO_2_ and FES-LEC only that had steady increases in just 60% and 80% peak VO_2_. The combination of ACE + FES-LEC demonstrates better oxygenation than either ACE or FES-LEC alone [66]. These forms of hybrid-FES training are more suited for high-intensity, high-volume exercise training than FES-cycling only and require intact upper extremity function.

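### The 90% power for glucose effectiveness rests on a one-arm pre-post change and is not the power to compare the two arms

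*Protocol article*

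**What the plan says.** The Statistical analyses section fixes the primary analysis: "A repeated-measures ANOVA will be performed with glucose effectiveness as the primary study outcome and effects for treatment group", time (baseline, P1 and P2), "and the interaction between the two factors included in the model". The objectives, at the end of the Background, compare NMES before FES-LEC with passive movement and FES.

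The Sample size section takes its effect from one regimen, NMES-RT: "Glucose effectiveness possesses the smallest effect size from baseline to follow-up with NMES-RT showing a mean baseline effectiveness of 0.01716" and a "post-treatment mean of 0.02258". With a variance of 0.0001 it reports f = 0.271. Adding a correlation of 0.3735 and three measurements, it concludes that "38 individuals will need to complete the study at 90% power using a Type-1 error rate of 0.05", and it recruits 48 to allow for 20% dropout. It gives no change in glucose effectiveness for a control group.

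For insulin sensitivity (f = 0.313) and VO2 (f = 0.432) it states powers of 97.51% and 99.82% "for observing the baseline to follow-up difference between the NMES + FES and Control + FES groups".

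**The concern.** In a randomised trial with a baseline and two follow-ups, the treatment effect in a repeated-measures ANOVA is carried by the group-by-time interaction. The effect size for that test must describe how much the arms differ in their change. A change seen in one treated group describes something else. When it is entered as the interaction effect, it stands for a between-arm difference about twice as large as the change itself. When it is entered as a time effect, the resulting power says nothing about the arms.

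The stake is the power claim for the primary outcome, on which the enrolment target is built. A reader of the results would judge them against a 90% that the design does not have for an effect of the pilot's size.

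**Working it through.** **Inputs from the Sample size section.** Means 0.01716 and 0.02258; variance 0.0001, so SD 0.01; correlation ρ = 0.3735; m = 3 measurements; α = 0.05; N = 38 completers; 20% dropout. Equal allocation (19 per arm) and a common correlation between all pairs of visits are assumed.

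**1. Where f comes from.** Change = 0.02258 − 0.01716 = 0.00542, which is 0.542 SD. Then f = 0.00542 / 0.01 / 2 = 0.271 exactly. No control mean is used.

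**2. Reproducing the stated N.** The G*Power form is λ = N·m·f² / (1 − ρ) = 38 × 3 × 0.271² / 0.6265 = 13.36.
- Within-between interaction, 2 groups, df 2 and 72: power 90.4% at 38 and 89.5% at 37.
- Within-subject time test: the same λ, and power again 90.4% at 38.
- Dropout: 38 / 0.8 = 47.5, rounded up to 48.

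The stated figures therefore reproduce, but they do not show which of the two tests was chosen.

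**3. The interaction effect for an assumed between-arm difference.** Let δ be the between-arm difference, in SD units, at baseline, P1 and P2. After the group and time main effects are removed, each of the six cells is left with ±(δ_j − mean δ)/2. So f is half the root mean square deviation of the three δ values. With the pilot gain d = 0.542 as the unit:

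| Between-arm difference (× 0.542 SD) at B, P1, P2 | f | Power at 38 |
|---|---|---|
| 0, 1, 1 (gain at P1, held) | √(1/18) × 0.542 = 0.128 | 30.7% |
| 0, 0.5, 1 (linear to P2) | √(1/24) × 0.542 = 0.111 | 23.9% |
| 0, 1, 0 (control catches up fully) | 0.128 | 30.7% |
| 0, 1, 0.5 (control catches up by half) | 0.111 | 23.9% |
| 0, 1, 1.5 (difference grows) | 0.312 × 0.542 = 0.169 | 50% |
| 0, 1, 2 (difference doubles) | 0.408 × 0.542 = 0.221 | 75% |

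A simulation of the planned ANOVA (20,000 runs, 19 per arm) gave 31.0% and 24.3% for the first two rows. In those two rows, 90% power would need 164 and 218 completers.

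**4. What 38 completers can detect.** Interaction power is 90% at f = 0.269. For a difference present at P1 and held at P2, that is 0.269 / √(1/18) = 1.14 SD, or 0.0114. Relative to the pilot gain this is 1.14 / 0.542 = 2.1 times.

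**5. The other two outcomes.** At N = 38 and ρ = 0.4, f = 0.313 and 0.432 give 97.3% and 99.98%, close to the stated 97.51% and 99.82%. If these f values are also one-arm changes (an assumption), the same conversion gives f = 0.128 to 0.148 and 0.176 to 0.204, and power of about 32–41% and 56–69%.

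**The case against.** Several points on the other side stand.

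- **The test is not named.** A reader might infer that f = 0.271 was demonstrably entered as an interaction effect. The time test gives the same 38, and the between-group wording is attached to insulin sensitivity and VO2, not to glucose effectiveness. The defect survives either way: if the time test was used, the 90% is not about the arms.
- **The 24–31% is not the trial's true power.** A reader might take it to follow from the plan's own inputs. It also needs an assumed control change and an assumed ceiling on the between-arm gain. The hypotheses in the Background expect prior NMES to enhance the gains made during FES-LEC, so the difference could grow after P1. The last two rows of the table allow for that and still fall short of 90%.
- **Control-arm FES-LEC does not by itself lower the power further.** The Discussion says that FES-LEC "effectively restores muscle size and improve of cardio-metabolic risk factors after SCI", which invites that inference. But both arms receive it, an equal gain cancels, and a full catch-up at P2 leaves the interaction f at 0.128.
- **Testosterone.** The Background describes reference [25] as 16 weeks of NMES-RT with testosterone, and [25] is cited for f and the variance. The means, however, are labelled as NMES-RT, and the article does not say outright that they came with testosterone. The source is unclear; contamination is not established.
- **Other analyses.** A baseline-adjusted comparison at one follow-up would give about 42% at 38 completers under the pilot-gain assumption. It is not the planned analysis, and it is also well below 90%.

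The article sets no rule for reading a null result, so nothing here shows that one would be misread.

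**Conclusion.** The point holds. The sums in the Sample size section are right; the effect put into them is the wrong kind. The 90% for glucose effectiveness comes from a one-arm change and is not the power of the planned comparison between arms. If the arms differ by the pilot gain, power at 38 completers is about 31% (gain at P1, held) or 24% (linear to P2). With a difference that grows to 1.5 or 2 times the pilot gain at P2 it is about 50% or 75%. All of these rest on assumed between-arm patterns, because the article states none, and on equal allocation with a common correlation of 0.3735. None of the patterns examined reaches 90%; that needs about 1.14 SD at both follow-ups.

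**What to change.** Keep the enrolment target and rewrite the power statement.

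1. Replace the one-arm effect with an assumed between-arm difference in change at P1 and P2, labelled as an assumption. Name the test (group-by-time interaction) and give its power at 38 completers in place of the 90%.
2. Alternatively, state that 38 completers give 90% power only for a between-arm difference in change of about 1.14 SD (0.0114) present at both P1 and P2, about 2.1 times the pilot gain.
3. Say how the f values for insulin sensitivity and VO2 were obtained. If they are one-arm changes, recompute 97.51% and 99.82% in the same way.
4. Identify the source of the pilot means, variance and f, and any treatment given alongside NMES-RT.

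The cost is a rewritten section and a much less favourable stated power. No participants, visits or measurements are added.
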